# Treatment of chronically depressed patients: A multisite randomized controlled trial testing the effectiveness of 'Cognitive Behavioral Analysis System of Psychotherapy' (CBASP) for chronic depressions versus usual secondary care

**DOI:** 10.1186/1471-244X-8-18

**Published:** 2008-03-25

## Abstract

**Background:**

'Cognitive Behavioral Analysis System of Psychotherapy' (CBASP) is a form of psychotherapy specifically developed for patients with chronic depression. In a study in the U.S., remarkable favorable effects of CBASP have been demonstrated. However, no other studies have as yet replicated these findings and CBASP has not been tested outside the United States. This protocol describes a randomized controlled trial on the effectiveness of CBASP in the Netherlands.

**Methods/Design:**

The purpose of the present paper is to report the study protocol of a multisite randomized controlled trial testing the effectiveness of 'Cognitive Behavioral Analysis System of Psychotherapy' (CBASP) for chronic depression in the Netherlands. In this study, CBASP in combination with medication, will be tested versus usual secondary care in combination with medication. The aim is to recruit 160 patients from three mental health care organizations. Depressive symptoms will be assessed at baseline, after 8 weeks, 16 weeks, 32 weeks and 52 weeks, using the 28-item Inventory for Depressive Symptomatology (IDS). Effect modification by co morbid anxiety, alcohol consumption, general and social functioning and working alliance will be tested. GEE analyses of covariance, controlling for baseline value and center will be used to estimate the overall treatment effectiveness (difference in IDS score) at post-treatment and follow up. The primary analysis will be by 'intention to treat' using double sided tests. An economic analysis will compare the two groups in terms of mean costs and cost-effectiveness from a societal perspective.

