#### Randomization

After signing the informed consent form, patients will enroll in the study and start with the baseline interview. After completing the baseline interview, patients will be assigned at random to either the intervention group or the control group. The intervention group will receive CBASP, while the control group will receive treatment as usual. Randomization will be performed by an external researcher using a computerized random number generator. Randomization is stratified per location.

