#### Assessments

Data are collected at five points in time: at baseline (T0), after 8 weeks of treatment (T1), after 16 weeks of treatment (T2), after 32 weeks of treatment (T3), and at the endpoint, after 52 weeks of treatment (T4). The Quick Inventory of Depressive Symptomatology self-report [23] will be assessed monthly. Table 1 summarizes the measures that are used at each point. The assessments will be performed by an experienced research nursing staff. At baseline and endpoint there will be a face-to-face interview besides the written questionnaires; the three assessments in between consist of written questionnaires only. The research nursing staff from the three participating organizations will participate in a two-day training course to make sure the measures are conducted the same way at the different locations.

**Table 1 T1:** Summary of measures

**Measure**	**Baseline**	**8 week follow-up**	**16 week follow-up**	**32 week follow-up**	**52 week follow-up**

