**Self report measurements:**					
Inventory of Depressive Symptoms (IDS)	x	x	x	x	x

Quick Inventory of Depressive Symptoms (QIDS)	Monthly assessment				

Beck's Anxiety Inventory (BAI)	x	x	x	x	x
AUDIT measure of alcohol consumption	x	x	x	x	x
Working alliance questionnaire-patient version		x	x	x	
Mastery scale measures locus of control	x	x	x	x	x
Social activity/participation	x	x	x	x	x
WHODAS	x	x	x	x	x
Loneliness & Affiliation Scale	x				x
NEO-Five Factor Inventory	x				x
Mood Disorder Questionnaire	x				x
Psychological Well Being (PWB)	x				x
Lack of Psychological Mindedness (LPM)	x				x
Remembered Parenting Scale (RRP)	x				

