**Questionnaires for economic evaluation:**					
Registration of usage medication	x				x
TIC-P measures illness and work	x				x
Perceived need for care	x				x
TIC-P work + health care utalization self report			x	x	

**Questionnaires filled in by therapists:**	**Baseline**	**8 week follow-up**	**16 week follow-up**	**32 week follow-up**	**52 week follow-up**

Clinical Global Impression-Improvement (CGI)		x	x	x	x
Working alliance questionnaire, therapist version		x	x	x	

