#### Secondary measures of outcome/predictors of response

To assess chronic depression and co morbid disorders at baseline and at the end of the study patients will receive a diagnostic interview using the M.I.N.I. plus [19,20].

Information on demographic factors (age, gender, marital status, education, professional occupation) will be collected in the baseline interview and at the end of the study.

Putative modifiers of effect are well known risk-factors for chronic depression [24], these are: level of functioning, which will be measured using the WHODAS [25], social contacts and social participation using the Loneliness & Affiliation Scale [26] and the Social Participation Scale [27], locus of control using the Mastery Scale [28] and psychological well being using the Psychological Well Being Scales (PWB) [29]. Physical health and diseases will be measured by a validated Dutch questionnaire [30], psychological mindedness using the Lack of Psychological Mindedness (LPM) [31] and parental relationship using the Remembered Parenting Scale (RRP) [31]. The Mood Disorder Questionnaire (MDQ) [32] will be used to measure bipolar symptoms, number of depressive episodes in the past five years using the Life Chart [33], anxiety using the Beck Anxiety Inventory (BAI) [34], alcohol dependence using the Alcohol Use Disorders Identification Test (AUDIT) [35], recent trauma using the Brugha questionnaire [36] and childhood trauma using the Nemesis questionnaire [37]. Personality will be measured using the NEO-Five Factor Inventory (NEO-FFI) [38] and working alliance using the Working Alliance questionnaire [39].

All measures of outcomes are widely used internationally, are reliable and valid, also for usage in the Netherlands.

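### Working alliance is listed as an effect modifier to be tested, but every alliance measurement falls after randomization, so the test cannot show a pre-treatment factor modifying the treatment effect

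*Protocol article*

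**What the plan says.** The abstract (Methods/Design) of the protocol article commits to a set of modifier tests: "Effect modification by co morbid anxiety, alcohol consumption, general and social functioning and working alliance will be tested".

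The section Secondary measures of outcome/predictors of response introduces its modifiers with "Putative modifiers of effect are well known risk-factors for chronic depression". The paragraph ends with personality and "working alliance using the Working Alliance questionnaire".

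Table 1 has two alliance rows, "Working alliance questionnaire-patient version" and "Working alliance questionnaire, therapist version". Each is marked at weeks 8, 16 and 32, and neither at baseline or week 52. Under Randomization, the order of events is: "After completing the baseline interview, patients will be assigned at random to either the intervention group or the control group".

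The Analysis section mentions neither alliance nor effect modification. It refers only to exploratory work on other explanatory factors.

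**The concern.** A test of effect modification asks whether the randomized effect differs between groups of patients defined before treatment. Alliance cannot define such groups here, because its first value is taken eight weeks into treatment. By then the assigned treatment, and the patient's early progress under it, may have changed the score.

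Two statements in the CBASP section make this more than a formality. The therapist relationship is one of the instruments of the therapy, and the early, more intensive phase may be extended when that relationship is hard to build. Alliance is thus something the experimental arm works on, and something that can alter how much therapy is given.

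A reported finding that CBASP works better in patients with a good alliance would be at stake. Readers would take it as guidance on whom to treat, although the score does not exist when treatment is chosen.

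**Working it through.** The plan states no figure for the modifier tests, so there is none to reproduce. The check is mainly a reading of the schedule, followed by a small illustration.

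**1. Timing**

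| Variable named in the abstract | Instrument | Baseline value in Table 1? |
|---|---|---|
| Comorbid anxiety | BAI | yes |
| Alcohol consumption | AUDIT | yes |
| General and social functioning | WHODAS, social participation, Loneliness & Affiliation Scale | yes |
| Working alliance | patient and therapist versions | no; weeks 8, 16 and 32 only |

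The blank baseline cell is unlikely to be a table-reading fault. Two separate rows agree, neighbouring rows carry all five marks, and an alliance with the study therapist cannot exist before treatment starts.

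**2. Why equal alliance scores do not mean comparable patients**

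All inputs in this step are assumed, in SD units; none comes from the documents. T is arm (1 = CBASP). U is prognosis, with the same distribution in both arms by randomization.

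- Alliance: A = 0.5·T + 0.5·U + noise, total within-arm SD 1.
- Outcome: Y = −0.5·T − 0.6·U + noise. The treatment effect is −0.50 for everyone, so there is no true modification.

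At a given score a, expected prognosis is 0.5·a in usual care and 0.5·(a − 0.5) in CBASP, a gap of 0.5 × (−0.5) = −0.25. That gap moves the outcome by −0.6 × (−0.25) = +0.15. The arm difference at equal alliance is therefore −0.50 + 0.15 = −0.35, not −0.50. Simulation (4,000 runs) gave −0.346 with 120 patients and −0.347 with 160. The interaction test itself rejected in 4.9% and 4.7% of runs, which is nominal.

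**3. When the interaction test itself rejects too often**

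This requires the alliance-outcome correlation to differ between arms. With 60 per arm (Sample size section), unit variances and assumed correlations r1 (CBASP) and r0 (usual care):

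z ≈ (r1 − r0) / √{[(1 − r1²) + (1 − r0²)] / 60}

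- r1 = 0.5, r0 = 0.2: 0.3 / √(1.71/60) = 0.3 / 0.169 = 1.78, so about 43% rejection (simulated 41%).
- r1 = 0.4, r0 = 0.2: 0.2 / √(1.80/60) = 0.2 / 0.173 = 1.15, so about 21% (simulated 21%).
- r1 = r0: z = 0, so 5% (simulated 5.5% at 0.3 in both arms).

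A second simulation, using the data model of step 2, gave 17% (0.6 in CBASP versus 0.3 in usual care) and 39% (0.7 versus 0.2) with 120 patients, and 21% and 49% with 160. A marker measured at baseline stayed at 4.5–5.7% throughout.

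These percentages are the power to detect a difference in correlation that was put in by assumption. They show what could happen if treatment changes how closely alliance follows outcome, and do not estimate an error rate for this trial.

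**The case against.** The strongest reply is that little is committed. The modifier label is explicit for alliance in one abstract sentence only. In the secondary-measures paragraph, the sentence that opens the modifier list names functioning, social contacts and participation, locus of control and well-being. Alliance comes at the end, under a heading that also covers secondary outcomes. The Analysis section specifies no interaction model, and an analysis plan not shown may. The second research question is about patient-related factors, and nothing says alliance is meant to answer it.

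Much of this stands as to weight. It does not remove the point: the abstract sentence is unqualified, and no later plan can supply a baseline alliance value.

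Three stronger readings are tempting, and the documents do not support them.

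- **A false-positive rate of 21–41%.** A reader might infer this from the illustration. No document figure supports unequal correlations, and without them the test stays near 5%.
- **The same fault in the BAI, AUDIT, WHODAS or Mastery scores.** All four have baseline values, and nothing says later values will serve as modifiers. Which visit enters the model is ordinary analysis-plan detail.
- **No comparable therapist in usual care.** The Treatment as usual section first names cognitive behavioural, interpersonal and short psychoanalytic supportive therapy; relaxation and running come under other possible components. Both arms also have clinical-management contacts with their medication.

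**Conclusion.** The point holds as a labelling and interpretation error in one stated secondary analysis. Working alliance is named as an effect modifier, the trial's own schedule makes it a post-randomization variable, and the experimental treatment acts on it. An arm-by-alliance term would therefore have no randomized interpretation and would not identify a patient factor available at the treatment decision.

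This conclusion rests on Table 1, the order of randomization and the description of CBASP, not on the simulations. Its size cannot be fixed from the documents. Under assumed inputs the interaction test ranges from nominal to badly misleading, and even where it is nominal the arm difference at equal alliance can depart from the randomized effect (−0.35 against −0.50 SD in the example).

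A reader might infer that the main result is at risk. It is not: the primary intention-to-treat comparison and the sample size do not involve alliance.

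**What to change.** - Remove working alliance from the effect-modifier list in the abstract, and describe it under secondary measures as a process variable.
- If it is analysed, do so as an exploratory process or mediation question: for example, week-8 alliance against later IDS change, adjusted for baseline and week-8 IDS. Table 1 already provides both measurements.
- State that the result is non-randomized evidence. Adjustment or a mediation method does not remove unmeasured confounding between alliance and outcome.
- Keep effect-modification tests to variables measured at baseline. The other modifiers named in the abstract already qualify.

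The cost is wording and one fewer advertised modifier. No new data, patients or visits are needed, and the planned 160 participants are unchanged.

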**Discussion:**

The study will provide an answer to the question whether the favorable effects of CBASP can be replicated outside the US.

**Trial Registration:**

The Dutch Cochrane Center, NTR1090.

## Background

According to the World Health Organization, Major Depressive Disorder (MDD) is the second largest healthcare problem worldwide in terms of limitations caused by illness [1]. MDD causes high rates of subjective suffering, absenteeism and utilization of medical services [2]. Both in the Netherlands and elsewhere it was found that 20% of depressions still persist after two years [3,4]. Chronic MDD causes a greater illness burden, more suicide attempts and more hospital admissions compared to acute MDD [5,6]. In outpatient mental health populations, chronic MDD affects an estimated 25–35% of depressive patients [7,8]. Unfortunately, the treatment results for this group of depressed patients are often disappointing and the existing treatment protocols are insufficiently tailored to chronic MDD [9]. For this reason, an effective psychotherapeutic treatment will constitute a welcome addition to the range of treatments currently available for chronically depressed patients.

Although there is a reasonably large body of literature evaluating cognitive as well as interpersonal therapy for nonchronic or mixed depressed samples, few studies have specifically investigated the group of chronically depressed patients [10]. A study that did target this group of patients examined the effectiveness of 'Cognitive Behavioral Analysis System of Psychotherapy' (CBASP), a form of psychotherapy that was specifically developed for chronic depression. CBASP's core procedure is called "situational analysis", a highly structured technique that teaches chronically depressed patients to fix their problematic interpersonal encounters. It is designed to teach patients that their behavior has consequences (called perceived functionality) by focusing on situational consequences to change their thoughts and behavior. CBASP conceptualizes that the interpersonal difficulties these patients encounter outside the therapy are also likely to emerge in the therapeutic relationship [11]. These difficulties are anticipated through "transference hypotheses" formulated early in treatment, which helps the therapist to recognize and resolve therapeutic impasses [9,12].

In a multisite trial involving 681 patients suffering from chronic depression, Keller and colleagues [13] compared the efficacy of an antidepressant (nefazodone), CBASP alone and their combination. After 12 weeks of treatment CBASP alone was equally effective as nefazodone alone [response rate of 48%]. The combination of nefazodone and CBASP was the most effective treatment [response rate of 73%]. After four months continuation treatment the authors found no difference between nefazodone and CBASP and found an ongoing advantage for combined treatment. Furthermore, over 85% of responders after 12 weeks of treatment maintained that response in continuation [14]. After 52 weeks of treatment, it was also found that CBASP was effective as a maintenance treatment for chronic depression [15].

In addition, it was found that CBASP was a good alternative for patients who were not motivated for, or refractory to medical treatment. For the non-responders in the study it was found that the switch from nefazodone to CBASP and vice versa resulted in clinically and statistically significant improvements [16,17].

As a result of these findings, CBASP is mentioned as an evidence based treatment option for chronic depression in the Dutch treatment guidelines [18]. However, the results of the American study have not yet been replicated. In addition, the dissemination of CBASP outside the US is limited. In order to test whether these findings can be replicated in a Dutch population we designed a randomized controlled trial on the effectiveness of CBASP. Our research questions are:

1. Is CBASP more effective and cost-effective than usual secondary care?

2. Which patient related factors predict a beneficial response?

## Methods/Design

### Study design

This study is a multi-center randomized controlled trial in which the effects of CBASP will be evaluated. CBASP, in combination with antidepressant treatment, will be tested versus usual secondary care in combination with antidepressant treatment over 52 weeks follow-up. The aim is to establish the clinical and cost effectiveness of CBASP plus antidepressant treatment in secondary care.

### Recruitment/Settings and locations

Patients will be recruited within the mood disorder departments of three organizations for mental health care in Amsterdam and The Hague. All newly registered patients will first be seen by a psychologist or psychiatrist for an intake and screening interview, which is part of a standard procedure. After the intake procedure patients' diagnosis and indication will be discussed in a staff meeting. At each site, the research-coordinator of the study will attend the staff meetings to select the patients diagnosed with chronic depression. These patients will be approached for participation in the study. The coordinator will be screening the patients on the inclusion-exclusion criteria of this study and inform them about the study. If patients are willing and eligible to participate, written informed consent will be elicited. The inclusion period will cover one year.

### Participants

#### Inclusion criteria

Patients (aged 18–65) are eligible to participate if their main diagnosis is a chronic form of depression according the DSM-IV criteria: a) a chronic major depressive disorder (i.e. existing for longer than 2 years) or b) a major depressive disorder superimposed on a dysthymic disorder or c) a recurrent major depressive disorder which, in the past 2 years, never fully remitted between the episodes. The Mini International Neuropsychiatric Interview plus (M.I.N.I. plus), a structured diagnostic interview developed in 1990 by psychiatrists and clinicians in the United States and Europe for DSM-IV and ICD-10 psychiatric disorders, will be used to assess chronic depression [19,20]. In addition, the level of symptom severity should be moderate to severe, expressed as a score of 22 or more on the 28-item Inventory for Depressive Symptomatology (IDS) [21,22].

#### Exclusion criteria

Patients are excluded from the study if: a) they suffer from one (or more) of the following disorders: a psychotic disorder, bipolar disorder, organic brain syndrome, substance dependence, or a severe borderline -, schizotypical -, or antisocial personality disorder or b) they have high risk of suicide c) they do not have sufficient command of the Dutch language necessary to participate in the study.

#### Randomization

After signing the informed consent form, patients will enroll in the study and start with the baseline interview. After completing the baseline interview, patients will be assigned at random to either the intervention group or the control group. The intervention group will receive CBASP, while the control group will receive treatment as usual. Randomization will be performed by an external researcher using a computerized random number generator. Randomization is stratified per location.

#### Assessments

Data are collected at five points in time: at baseline (T0), after 8 weeks of treatment (T1), after 16 weeks of treatment (T2), after 32 weeks of treatment (T3), and at the endpoint, after 52 weeks of treatment (T4). The Quick Inventory of Depressive Symptomatology self-report [23] will be assessed monthly. Table 1 summarizes the measures that are used at each point. The assessments will be performed by an experienced research nursing staff. At baseline and endpoint there will be a face-to-face interview besides the written questionnaires; the three assessments in between consist of written questionnaires only. The research nursing staff from the three participating organizations will participate in a two-day training course to make sure the measures are conducted the same way at the different locations.

**Table 1 T1:** Summary of measures

**Measure**	**Baseline**	**8 week follow-up**	**16 week follow-up**	**32 week follow-up**	**52 week follow-up**
**Interview:**					
Mini plus measures diagnostics	x				x
Demographics	x				x
CBS questionnaire measures physical health	x				x
LIFE-CHART measures duration of depression	x				
NEMESIS questionnaire of childhood trauma	x				
Brugha questionnaire of recent life events	x				x
**Self report measurements:**					
Inventory of Depressive Symptoms (IDS)	x	x	x	x	x

Quick Inventory of Depressive Symptoms (QIDS)	Monthly assessment				

Beck's Anxiety Inventory (BAI)	x	x	x	x	x
AUDIT measure of alcohol consumption	x	x	x	x	x
Working alliance questionnaire-patient version		x	x	x	
Mastery scale measures locus of control	x	x	x	x	x
Social activity/participation	x	x	x	x	x
WHODAS	x	x	x	x	x
Loneliness & Affiliation Scale	x				x
NEO-Five Factor Inventory	x				x
Mood Disorder Questionnaire	x				x
Psychological Well Being (PWB)	x				x
Lack of Psychological Mindedness (LPM)	x				x
Remembered Parenting Scale (RRP)	x				
**Questionnaires for economic evaluation:**					
Registration of usage medication	x				x
TIC-P measures illness and work	x				x
Perceived need for care	x				x
TIC-P work + health care utalization self report			x	x	

**Questionnaires filled in by therapists:**	**Baseline**	**8 week follow-up**	**16 week follow-up**	**32 week follow-up**	**52 week follow-up**

Clinical Global Impression-Improvement (CGI)		x	x	x	x
Working alliance questionnaire, therapist version		x	x	x	

